## Abstract

Anorexia nervosa (AN) is a life-threatening disorder with peak onset during adolescence. Prior research supports the effectiveness of family-based treatment (FBT) for AN in adolescents, but studies do not regularly include neuroimaging to investigate the effects of FBT on the brain. This is important because we know that malnutrition has a detrimental impact on brain volume, cortical thickness, and function, which often recover with weight restoration. Additionally, early weight gain in FBT has emerged as a robust predictor of treatment outcome, yet it is unclear whether it is associated with neural change. Understanding neural change during treatment, particularly in the early weeks, has the potential to improve outcome by enhancing motivation for rapid behavior change, while also highlighting mechanisms by which early treatment response leads to improved outcome. This manuscript describes a study protocol and discusses both challenges and implications for this type of integrative research.

## Introduction

### Background and Rationale for Studying Early Neural Change in Adolescent AN

Family-based treatment (FBT) for adolescent anorexia nervosa (AN) results in clinically significant improvement in about 75% of patients and remission in between 22%–49% by the end of treatment (EOT) (1). Despite this, these numbers demonstrate that a percentage of patients do not achieve optimal outcome. Prior research has identified early weight gain of 2.4 kg by session 4 in FBT as a surrogate early marker for full weight restoration [>94% expected body weight (EBW)] by end of treatment (EOT) (2–6). An improved understanding of the neural underpinnings of early weight gain could be helpful in identifying treatment mechanisms and developing novel ways to improve FBT through behavioral reinforcement or support of refeeding effects, which will ultimately result in higher rates of recovery and decreased use of higher cost and potentially ineffective programs.

Existing randomized controlled trials (RCTs) have understandably focused attention on clinical outcomes such as weight gain and behavioral and attitudinal changes in the patients and their families (7). However, adding neuroimaging to an RCT would allow us to examine neural change over the course of treatment with particular emphasis on early neural changes. Determining neural correlates of the robust marker of early weight gain can potentially help us understand why it results in improved outcome and will allow us to further enhance treatment for those who do not show this early response. For example, the predictive effect of early treatment response may simply reflect that most change occurs early in treatment or it could be that early changes lead to neural changes that make further treatment more effective. Parents who understand the impact of their early efforts in refeeding on their children’s brains may be more motivated to make necessary changes early in treatment. Given anecdotal evidence that many parents are resistant to pushing rapid weight gain to reduce conflict during meals or make meals easier, this could be especially helpful. Further, clinically, we see many parents concerned about a focus on feeding while seemingly ignoring cognitive symptoms. Providing evidence of brain effects of early refeeding efforts can assuage this concern and motivate parental feeding.

### Prior Evidence of Change Neural Differences in AN With Recovery

There are currently no studies of brain changes over the course of FBT and no studies of brain change examining early weight change. Most studies that have investigated structural and functional brain changes with treatment have focused on weight restoration in hospital settings (8, 9). A recent study examined change in cortical thickness with short-term weight recovery and found significant change with improvements in nutrition (10). Because early weight gain in FBT is likely a consequence of consistent nutrition *via* refeeding, there may be significant brain change in early responders that influence later treatment outcome.

#### Structural

In addition to structural improvements such as brain volume (9) and cortical thickness (10), diffusion tensor imaging (DTI) studies suggest that dysfunction in brain networks in AN may be relate to reduction of myelin that surrounds the axons of neurons (11). Myelin is made of fatty acids, and thus, severe dietary (especially fat) restriction may result in deterioration of the myelin. As nutrition improves, myelination may also improve, impacting white matter integrity. Seitz and colleagues have recently conducted a meta-analysis on white matter volume in AN and found that reductions in white matter volume appear to normalize with recovery (9). Importantly, white matter volume loss predicted BMI at 1-year follow-up after hospitalization, suggesting that this is a marker for longer-term risk (12). Thus, in addition to examining change in white matter integrity during treatment, it would be useful to also investigate whether it predicts treatment response.

#### Intrinsic Connectivity Networks (Resting-State fMRI)

As a consequence of the shifts in white matter integrity, another likely area of change with recovery relates to network connectivity in the brain. Resting-state functional magnetic resonance imaging (r-fMRI) is a tool that allows us to understand how brain activity is organized into coherent and temporally correlated networks of brain regions (13). These networks, often referred to as intrinsic connectivity networks (ICNs), are consistent, have high test-retest reliability (14) and correspond with structural pathways (15). Various differences in ICN activity and connectivity relate to psychopathology and mood states (16). Two such ICNs have often been identified in psychopathology research, including in AN. The default mode network (DMN) was one of the first ICNs identified and its activity correlates with baseline non-task activation and is often implicated in self-referential processes (17). The salience network (SN) is involved in integrating information between a number of systems and involves connections between the dorsal anterior cingulate cortex and frontoinsular brain regions, as well as amygdala and ventral tegmental area, important for emotion and reward detection (16). Given the symptom-related features of self-relevant thoughts (related to body shape/weight, general self-esteem, etc.), as well as processing internal and external stimuli to make eating decisions, these ICNs seem particularly relevant in AN. Indeed, McFadden and colleagues found reduced SN and DMN activity in women with AN (18). Individuals recovered from AN showed DMN and SN activity somewhere between acutely ill and healthy controls, with a significant difference remaining between recovered and control groups in SN activity (18). However, the timeline of these changes from acute illness to recovery are unknown. Network activity can reflect ongoing brain processes at rest dispersed across a network, whereas functional connectivity, the synchronous activity between regions in a network, can reflect longer term activity such that those regions may have stronger connections due to frequent co-activation (19). When looking at functional connectivity rather than overall activity of the network, there is evidence of increased connectivity in the DMN in AN (20, 21). Although the activity across the DMN may be reduced in AN at rest, this may reflect difficulty with ceasing engagement of task-like processing (perhaps related to perseverative thinking about food, weight, etc.). However, connectivity between regions within the DMN may be strengthened due to frequent co-activation outside of rest, such as during self-referential processing throughout the day. No studies to date have looked at change in these networks over the course of treatment, but there is evidence that psychotherapeutic interventions can result in change in functional connectivity in brain networks in other patient populations (22, 23). It is also possible to utilize functional connectivity in these networks to predict treatment outcome, as connectivity in the DMN has been a consistent neural marker and predictor of treatment response in depression (24, 25).

#### Task-Based Neural Function: Set-Shifting and Fear Response to Food

Furthermore, numerous studies have investigated task-based neural activity in AN, which may relate to the illness. These are studies that have utilized fMRI to measure brain activity during specific tasks to understand neural correlates of cognitive and emotional processes. Research suggests that patients with AN have difficulty with set shifting or task switching (26). Patients often perform slower on Trail B of the Trail Making Test, make more perseverative errors on the Wisconsin Card Sorting Test, and make more errors on the Brixton Task (27), although results are not always consistent. Neuroimaging studies suggest that these difficulties may reflect neural processing differences in the prefrontal cortex and precuneus (28–30). A recent study showed task shifting deficits in acutely ill patients, but not those recovered from AN (31). Indeed, longitudinal studies show that many of these deficits improve with weight restoration (32), and performance on set-shifting tasks improved with cognitive remediation therapy (33), but it is unclear how this may change in the context of FBT and relate to early treatment response. Importantly, a recent study of adolescents with AN showed that neural differences during set shifting when acutely ill were no longer present after 6 months and renutrition (34). Based on this literature of improvements with recovery, we predict change with FBT for both patients with early treatment response or those who make gains over the full course of treatment.

In addition to set shifting deficits, there is evidence of greater activation in the amygdala in response to images of high-calorie beverages and high-calorie foods (35–37). In anxiety disorders, pre-treatment amygdala activity predicts measures of post-treatment improvement in children and adults (38, 39), and amygdala hyperfunction normalizes after exposure-based treatment in specific phobia (40). Considering that successful refeeding represents repeated exposure to feared stimuli (food) in AN, amygdala response to food images may normalize in those who respond to treatment.

#### Behavioral Function: Inhibited Risk-Taking

Harm avoidance is frequently associated with AN (41). This may drive food restriction due to avoidance of potential weight gain, which patients perceive as negative. This harm avoidance may reduce risk-taking (42), which has been found in prior research in individuals with AN (43). Although most prior research on risk-taking in AN has used the Iowa Gambling Task, evidence suggests that it is not a reliable measure of risk-taking (44). Thus, other measures, such as the Balloon Analogue Risk Task used previously in AN (43) or the Angling Risk Task (45) may provide stronger evidence of inhibited risk-taking in AN (45, 46). We will explore risk-taking using the Angling Risk Task outside of the scanner with plans to obtain neuroimaging correlates in the future if the behavioral data support the initial hypothesis of change with weight gain during treatment.

### Specific Aims and Hypotheses

Overall, the study aims to examine the neural correlates of early weight gain in adolescents with AN undergoing FBT with MRI scans conducted at baseline prior to initiating treatment, after session 4 (the point at which weight gain is predictive of clinical EOT response), and again at EOT (18 sessions of treatment, approximately 6 months with a maximum of 9 months). Although this study is designed to provide evidence of feasibility in conducting neuroimaging in the context of FBT and establish preliminary effect sizes to guide future research, we provide the following specific hypotheses that we hope to explore in this pilot study. We hypothesize greater increases in brain volumes, surface area, and cortical thickness from pre-treatment to session 4 in those who gain more than 2.4 kg during that time. We also hypothesize that network connectivity and activity during r-fMRI will show greater changes in adolescents with early weight gain compared to those who do not show early weight gain. Specifically, we predict greater increases in default mode activity and reductions in SN activity from pre-treatment to session 4 in those who gain more than 2.4 kg during that time (47). We also hypothesize improvements in white matter integrity, measured with DTI, in those who gain more than 2.4 kg by session 4 compared to those who do not, providing evidence that consistent nutritional improvements can have rapid impact on brain connectivity (48). We also hypothesize improvements in functional tasks related to cognitive and emotional functioning in those who gain more than 2.4 kg by session 4. Specifically, we expect improvements in a task-switching task as evidenced by improved behavioral performance and altered brain activity in prefrontal cortex and superior parietal cortex. During a food image task, we expect to find reduced amygdala activity in response to food versus non-food images over time in those who show early weight gain. Although the primary aim relates to neural changes at session 4 (the time where early weight gain is predictive of outcome), a secondary aim is to examine these measures at EOT, which will allow us to capture any neural changes that may be more delayed, requiring longer length of time or more weight gain for recovery. This secondary aim is in place due to the preliminary nature of the protocol, since there is no prior research related to early treatment effects. In other words, this aim increases the likelihood to detect effects given that prior research on weight restoration in AN has shown improvements across these domains.

## Methods

### Participants

Participants for this study will be recruited directly from an existing RCT. The RCT is testing an adaptation to standard FBT wherein adolescents who do not gain 2.4 kg by session 4 are randomly assigned to either continue standard FBT or to receive Intensive Parent Coaching (IPC) which involves an additional intense scene during session 4 to increase urgency to act in the parents, a parent-only session to further support parental behavior change for refeeding, and an additional family meal for greater support and guidance of parent refeeding behaviors. Prior research informed the selection of 2.4 kg as the marker of early treatment response. Five studies identified early weight gain in FBT as a possible marker of early treatment response (2–4, 6, 49) converging on a consistent weight gain range of 2–3 kg by session 4. Unpublished data on early response from the largest multi-site study of FBT for adolescent AN (2) matched the weighted average of the current published studies, a weight gain of 2.4 kg by session 4. An additional study by Hughes and colleagues (50) found that 2.8 kg by session 5 was the most sensitive predictor of remission. However, this study involved twice weekly sessions for the first 2 weeks with session 5 occurring on week 3 of treatment (unlike 1 session per week in other trials). This increased intensity of treatment delivery may have shifted the timing and amount of early weight gain predictive of remission by end of treatment (50). Thus, the proposal settled on 2.4 kg by session 4 as the marker of early response. Importantly, we considered the use of change in percentage ideal body weight or BMI-SDS (body mass index standard deviation score) per age, but the prior research showed these predictive effects with the actual weight gained regardless of initial weight, height, age, or sex.

Because participants will be recruited for the neuroimaging study prior to the start of treatment, we cannot balance the numbers of participants in a particular treatment arm. All study participants who meet eligibility criteria and are able to visit Stanford University for three imaging appointments will be invited to participate. Although the main RCT is being conducted at two sites (Stanford University and University of California, San Francisco), they are both located in the San Francisco Bay Area, and thus, are both potential sites for the recruitment of participants for this neuroimaging component. The population of the Bay Area is large and diverse, and the RCT makes specific efforts to recruit minorities for the study. The target sample size for this preliminary study is 20 in order to establish feasibility of including neuroimaging to an RCT of FBT and obtain preliminary effect sizes. Inclusion criteria include: 12–18 years of age that meet DSM-5 criteria for AN and participating in the RCT testing IPC for early non-response to FBT. Exclusion criteria include: 1) associated physical illness that necessitates hospitalization; 2) psychotic illness or other mental illness requiring hospitalization; 3) current dependence on drugs or alcohol; 4) physical conditions (e.g., diabetes mellitus, pregnancy) known to influence eating or weight; 5) Wechsler Abbreviated Scale of Intelligence (WASI) scores below the low average range defined by the test (<80); 6) family history or current child abuse or neglect (when reported in response to a question on phone screen, the perpetrator of abuse is excluded from family treatment, but the adolescent may participate with the rest of the family); 7) previous FBT for AN; 8) contraindications for MRI (e.g., orthodontia, metallic implants); 9) current or past major neurological (e.g., seizure disorder, psychosis, head trauma) or major sensory deficit. Participants are withdrawn from the study if any of the following occur: 1) sexual or physical abuse by a family member; 2) hospitalization for >21 days; 3) missing >4 consecutive appointments; worsening of psychiatric conditions such that participant would be clinically better served by referral for other treatment; 4) participant undertaking other psychotherapies during the treatment study. Visual acuity is determined by self-report, and participants with corrected vision use MR-safe lenses during scans.

### Procedure

Assessments for the main RCT will be conducted at six major timepoints (baseline, 3-month mid-treatment, EOT (maximum of 9 months), and at 6- and 12-month follow-up). These assessments will include measures of weight, parental measures, and other psychopathology variables. Weekly assessment of weight and parent factors will also be conducted. For the neuroimaging study, we invite participants to have MRI and fMRI scans at baseline, session 4 mid-treatment, and EOT. All assessors are trained to reliability in the Eating Disorder Examination (EDE) (51) and other clinical diagnostic interviews, including the Kiddie Schedule for Affective Disorders and Schizophrenia (K-SADS) (52).

Neuroimaging sessions consist of structural, diffusion-weighted, and functional scans (one resting-state and two task-based). We use a 3T GE signa scanner to collect functional and anatomical imaging data. Visual stimuli are presented with a digital projector/reverse screen display system. Echo spiral imaging is used to measure the blood oxygen level dependent (BOLD) signal as an indication of cerebral brain activation. Images consist of 31 axial slices (4.0 mm with 0.5 mm gap) covering the whole brain (RT = 2 s, echo time = 30 ms, flip angle = 80, interleave = 1, FOV = 22 cm, matrix = 64 × 64). To reduce blurring and signal loss from field inhomogeneities, an automated high-order shimming method based on spiral acquisitions is used before acquisition of functional scans. R-fMRI scans consist of 240 volumes acquired over 8 min. Functional scans during the task-based paradigms will be acquired over approximately 22 min (task switching) and 8 min (food image task). Motion is measured immediately following functional scans, and the experiment is rerun if motion exceeds 1 mm. A diffusion-weighted scan (DTI) is collected with 37 diffusion directions (FOV = 22 cm, 2.3 mm slices). A high-resolution T1-weighted three-dimensional inversion recovery spoiled gradient-recalled acquisition in the steady state MRI sequence is used (inversion time = 400 ms, RT = 8 ms, echo time = 3.6 ms, flip angle = 151, FOV = 24 cm, 124 slices in coronal plane, matrix = 256 × 192, number of excitations = 2; acquired resolution = 1.5 × 0.9 × 1.1 mm). Images are reconstructed as a 124 × 256 × 256 matrix. We preprocess all data within 1-week of the scan to ensure that all the data are usable. We rescan subjects for whom we have poor data on structural and resting state scans.

#### Task Switching Task

We utilize a hybrid block and event-related design to examine task switching, which has been previously validated (53). This design allows for the separation of neural activity related to the cognitive load of engaging in task switching over a sustained period (block contrast) from the neural activity related specifically to the transient behavior of switching tasks on a particular trial (event-related contrast). Thus, we present blocks of mixed-task trials and blocks of single-task trials. The task requires participants to classify colored shapes (red and blue triangles and circles) based on groupings indicated by a written instruction, such as “Shape” or “Color.” In the mixed-task trials, classification task of the trial are randomly intermixed throughout the block. We present 50 mixed-task trials and 50 single-task trials. This task is delivered in 2 11-min runs, and engagement will be confirmed *via* confirmation of accuracy greater than 80%.

#### Food Image Task

We utilize the same design as in prior literature examining neural response to food images in AN by presenting five blocks of high-calorie food images alternating with five blocks of non-food images (37). Each block consists of 10 images presented for 1.5 s. Participants are instructed to look at each picture attentively. Images are rated after scanning for disgust and fear on a visual analog scale. This task takes approximately 8 min.

#### Risk-taking Task

In addition to the in-scanner tasks, after the scan, participants complete the Angling Risk Task (45) *via* Experiment Factory online (54). During the ART, participants fish for 30 rounds in a pond with different numbers of fish, mostly red fish with one blue fish. Each time the participant selects “Go Fish,” they randomly catch a fish in the pond. Each red fish results in points which can be collected when the participant selects “Collect” and moves on to the next round of fishing. However, if the participant catches the blue fish, the round will end, and the participant will lose all the points earned that round. Participants are told that to keep their points from round to round, they must stop fishing and press “Collect” before they catch a blue fish. There are two tournaments; one in which fish are released back to the pond after being caught, which results in the same number of red and blue fish throughout the round (Catch N Release). In the Catch N Keep tournament, caught fish come out of the lake, thus increasing the chance of catching a blue fish. The points earned in one tournament have no effect on the next, and participants are instructed to try to do as well as possible in both tournaments. Each red fish caught (point) is worth 2 cents, which is added up to a total dollar amount that participants can win at the end of the task (up to $25).

Both this neuroimaging study and the larger RCT have approval from the local Institutional Review Boards.

### Data Analytic Plan

Images will be preprocessed using *fMRIPprep* 1.2.3 (55, 56), which is based on *Nipype* 1.1.6-dev (57, 58).

#### Anatomical Data Preprocessing

All T1-weighted (T1w) will be corrected for intensity non-uniformity (INU) using N4BiasFieldCorrection (59) (ANTs 2.2.0). A T1w-reference map will be computed after registration of all T1w images (after INU-correction) using mri_robust_template [(FreeSurfer 6.0.1, (60)]. The T1w-reference will then be skull-stripped using antsBrainExtraction.sh (ANTs 2.2.0), using OASIS as target template. Brain surfaces will be reconstructed using recon-all [FreeSurfer 6.0.1, (61)], and the brain mask estimated previously will be refined with a custom variation of the method to reconcile ANTs-derived and FreeSurfer-derived segmentations of the cortical gray-matter of Mindboggle (62). Spatial normalization to the ICBM 152 Nonlinear Asymmetrical template version 2009c (Fonov et al., 2009, RRID : SCR_008796) will be performed through nonlinear registration with antsRegistration [ANTs 2.2.0, (63)], using brain-extracted versions of both T1w volume and template. Brain tissue segmentation of cerebrospinal fluid (CSF), white-matter (WM) and gray-matter (GM) will be performed on the brain-extracted T1w using fast [(FSL 5.0.9, (64)].

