#### Functional Data Preprocessing

For each BOLD run per subject (across all tasks and sessions), the following preprocessing will be performed. First, a reference volume and its skull-stripped version will be generated using a custom methodology of *fMRIPrep*. The BOLD reference will then be co-registered to the T1w reference using bbregister (FreeSurfer) which implements boundary-based registration (65). Co-registration will be configured with nine degrees of freedom to account for distortions remaining in the BOLD reference. Head-motion parameters with respect to the BOLD reference (transformation matrices, and six corresponding rotation and translation parameters) are estimated before any spatiotemporal filtering using mcflirt [(FSL 5.0.9, (66)]. The BOLD time-series (including slice-timing correction when applied) will be resampled onto their original, native space by applying a single, composite transform to correct for head-motion and susceptibility distortions. These resampled BOLD time-series will be referred to as *preprocessed BOLD in original space*, or just *preprocessed BOLD*. The BOLD time-series are resampled to MNI152NLin2009cAsym standard space, generating a *preprocessed BOLD run in MNI152NLin2009cAsym space*. First, a reference volume and its skull-stripped version are generated using a custom methodology of *fMRIPrep*. Several confounding time-series are calculated based on the *preprocessed BOLD*: framewise displacement (FD), DVARS and three region-wise global signals. FD and DVARS are calculated for each functional run, both using their implementations in *Nipype* [following the definitions by Power and colleagues (67)]. The three global signals are extracted within the CSF, the WM, and the whole-brain masks. Additionally, a set of physiological regressors re extracted to allow for component-based noise correction [*CompCor*, (68)]. Principal components are estimated after high-pass filtering the *preprocessed BOLD* time-series (using a discrete cosine filter with 128s cut-off) for the two *CompCor* variants: temporal (tCompCor) and anatomical (aCompCor). Six tCompCor components are then calculated from the top 5% variable voxels within a mask covering the subcortical regions. This subcortical mask is obtained by heavily eroding the brain mask, which ensures it does not include cortical GM regions. For aCompCor, six components are calculated within the intersection of the aforementioned mask and the union of CSF and WM masks calculated in T1w space, after their projection to the native space of each functional run (using the inverse BOLD-to-T1w transformation). The head-motion estimates calculated in the correction step are also placed within the corresponding confounds file. The BOLD time-series, are resampled to surfaces on the following spaces: *fsaverage5*. All resamplings can be performed with *a single interpolation step* by composing all the pertinent transformations (i.e., head-motion transform matrices, susceptibility distortion correction when available, and co-registrations to anatomical and template spaces). Gridded (volumetric) resamplings will be performed using antsApplyTransforms (ANTs), configured with Lanczos interpolation to minimize the smoothing effects of other kernels (69). Non-gridded (surface) resamplings were performed using mri_vol2surf (FreeSurfer).

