
Many internal operations of *fMRIPrep* use *Nilearn* 0.4.2 (70), mostly within the functional processing workflow. For more details of the pipeline, see the section corresponding to workflows in *fMRIPrep*’s documentation.

Structural measures of total gray matter volume, white matter volume, cortical surface area, and average cortical thickness will be extracted from FreeSurfer (run during preprocessing). After preprocessing, independent component analysis (ICA) will be conducted using FSL’s MELODIC software to examine intrinsic connectivity networks in r-fMRI. ICA is a statistical technique that separates a set of signals into independent spatiotemporal components (71). It allows for the removal of artifact and the isolation of neural networks (72, 73). We will allow the software to estimate the optimal number of components for each subject. Components will be transformed to standard space, and the DMN and SN will be selected from among each subject’s independent components using an automated template-matching procedure (73). A one-sample t-test will be performed on normalized network maps. These maps will be used to generate connectivity scores for each ICN.

Condition effects for the task-based fMRI will be estimated using the general linear model. The response to events will be modeled by a canonical hemodynamic response function (HRF). The task switching task has two events of interest: task-switch events and task-repeat events contrasted with each other, as well as two blocked conditions: mixed-task blocks and single-task blocks in another contrast. The food image task has two events of interest: food images and non-food images contrasted with each other. Condition-specific estimates of neural activity (betas, corresponding to the height of the HRF) will be computed independently at each voxel for each subject. Analyses will be conducted in FSL FEAT, which utilizes cluster-based thresholding and Gaussian Random Field (GRF) theory to identify significant clusters of voxels for each analysis. Although we have hypotheses related to certain brain regions, we will conduct whole brain analyses to ensure we are not biasing results.

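### The structural outcomes are taken from a FreeSurfer run on what reads as one T1w reference built from all T1w images, which conflicts with the per-visit values that the change hypotheses need

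*Protocol article*

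**What the plan says.** All references are to the protocol article.

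- **Anatomical reference** (Anatomical Data Preprocessing): "A T1w-reference map will be computed after registration of all T1w images (after INU-correction) using mri_robust_template". The text speaks of one map and does not split the images by visit. The map is then skull-stripped.
- **Surface reconstruction** (same section): "Brain surfaces will be reconstructed using recon-all", and "the brain mask estimated previously will be refined with a custom variation of the method to reconcile ANTs-derived and FreeSurfer-derived segmentations".
- **Functional data** (Functional Data Preprocessing): "For each BOLD run per subject (across all tasks and sessions), the following preprocessing will be performed". Each BOLD reference is then co-registered to the T1w reference, in the singular.
- **Source of the structural outcomes** (paragraph on structural measures, after the functional pipeline): grey and white matter volume, "cortical surface area, and average cortical thickness will be extracted from FreeSurfer (run during preprocessing").
- **Hypothesis** (Specific Aims and Hypotheses): "We hypothesize greater increases in brain volumes, surface area, and cortical thickness from pre-treatment to session 4", in those who gain more than 2.4 kg. The same measures at end of treatment (EOT) are a secondary aim.
- **Analysis** (end of the Data Analytic Plan): change over time in all measures is modelled with repeated-measures or mixed-effects methods. Baseline measures are explored as predictors of early response and of EOT outcome.
- **Scans** (Procedure): baseline, session 4 and EOT. One T1w sequence is described, poor structural scans are repeated, and preprocessing follows each scan within a week as a check that the data are usable.

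**The concern.** A merged within-subject T1w reference is a sensible common target for registering BOLD runs from several visits. It is not a suitable source for an outcome that is meant to change between those visits, because merging averages away the difference that the study wants to measure.

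The article names the FreeSurfer run inside preprocessing as the source of the structural outcomes. The only such run it describes sits in a sequence that starts from a single reference made from all T1w images. No section describes a reconstruction for each visit, or a longitudinal stream, for these outcomes.

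Structural change to session 4 is the first hypothesis listed, at the timepoint of the primary aim. The study is meant to supply preliminary effect sizes for later work. Followed literally, the pipeline would supply none for these measures, or would supply diluted ones. The exploratory prediction analyses would also be affected, because a structural value labelled baseline could contain images taken after treatment began.

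**Working it through.** The article gives no figure to reproduce. The check traces the images through the stated steps and counts values.

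**Does the merged reference feed FreeSurfer?** The article does not name the input to recon-all. It does say that the brain mask estimated earlier, from the T1w reference, is reconciled with the FreeSurfer segmentation. That step makes sense if both describe the same image.

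**Do all T1w images span visits?** This is not stated either. One T1w sequence is described per scan session, and repeats are made only for poor data, so several T1w images per subject arise mainly from the three visits. The functional section covers runs across all sessions and refers to one T1w reference, which fits pooling.

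**Values per structural measure** (target sample 20, three visits):

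| Reading | Values per subject | Observations | Within-subject changes from baseline |
|---|---|---|---|
| Visits pooled | 1 | 20 × 1 = 20 | 0 |
| One reconstruction per visit | 3 | up to 20 × 3 = 60 | 2 (session 4, EOT) |

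**If preprocessing is rerun as scans accrue, each time with all images so far.** Assume, for illustration only, that a measure from the merged image is the equally weighted mean of the per-visit values B (baseline), S (session 4) and E (EOT).

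- Session 4: (B + S)/2 − B = (S − B)/2, which is half the true change.
- EOT: (B + S + E)/3 − B = [(S − B) + (E − B)]/3. If all the change has occurred by session 4 (S = E), this is 2/3 of the true change. If none has (S = B), it is 1/3.

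The real merging and segmentation need not be linear, so these fractions show direction and rough size only.

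**Baseline predictors.** With all three visits pooled, up to 2 of the 3 images behind a baseline value postdate the start of treatment.

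**Share of outcomes.** The measures listed at the end of the Data Analytic Plan, with the task contrasts counted individually, are grey matter volume, white matter volume, surface area, thickness, salience network, default mode network, fractional anisotropy, R1, switch versus repeat, mixed versus single, food versus non-food, and risk-taking. That is 12, of which the first 4 come from FreeSurfer.

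**The case against.** The strongest reply rests on the Procedure section. Data preprocessed within a week of the baseline scan cannot include session 4 or EOT images, since EOT is about 6 and at most 9 months away. On that timetable a FreeSurfer run exists for baseline alone. Merging T1w images could then refer to repeat scans at one visit, and the whole article would be consistent. The phrase about all sessions qualifies BOLD runs and says nothing direct about pooling T1w images. The closing analysis paragraph plainly intends a score at each timepoint, and a condensed article often leaves out how a pipeline was run.

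Much of this stands. Pooling across visits and the input to recon-all are both inferred, and the one-week rule is in real tension with pooling. A reader might infer that structural change cannot be computed in this study, or that the investigators certainly merge visits. The documents support neither: each visit's images are acquired separately and survive, and a per-visit reading remains open.

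The reply does not remove the conflict. The one-week step has a stated purpose, checking usability, and nothing says that outcome values come from those runs or that each run is limited to one visit. Nor is this simply an omission, because the article does name the source of the structural outcomes and describes that source with a single reference.

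It can also be said that an analyst would notice one row per subject and rerun the data. That holds for full pooling. It does not hold for accruing reruns, which give three plausible rows per subject with the dilution hidden.

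**Conclusion.** The point holds as a conflict between stated steps. The anatomical pipeline and the source named for the structural outcomes, read literally, do not deliver the per-visit values that the aims and the analysis require. Under full pooling there is one blended value per subject and no change to analyse. Under accruing reruns, change to session 4 is about half its true size on the illustrative equal weighting.

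This rests on two inferences, that all T1w images spans a subject's visits and that recon-all uses the merged reference. Both are the most natural reading, but neither is stated word for word, so confidence is moderate. If anatomical processing is in fact run separately at each visit, the defect is one of wording.

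The scope is limited to four of twelve outcomes. The functional, diffusion and risk-taking measures still have a value at each visit. It nevertheless deserves correction before analysis, because it touches the first-listed hypothesis and the baseline predictors.

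**What to change.** State in the analysis plan that:

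1. any T1w reference merged across visits is used only for functional co-registration and normalisation;
2. grey and white matter volume, surface area and cortical thickness come from a separate recon-all on each visit's T1w data;
3. these per-visit values enter the mixed model;
4. the prediction analyses use structural values from the baseline visit only.

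Following the per-visit runs with FreeSurfer's longitudinal stream would be preferable, but independent per-visit runs already resolve the conflict. If the work is already done this way, the same statement settles the ambiguity. The cost is a short addition to the text and extra computing time, with no new scans.
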